## Abstract

**Introduction:**

Musculoskeletal system gradually degenerates with aging, and a hypoxia environment at a high altitude may accelerate this process. However, the comprehensive effects of high-altitude environments on bones and muscles remain unclear. This study aims to compare the differences in bones and muscles at different altitudes, and to explore the mechanism and influencing factors of the high-altitude environment on the skeletal muscle system.

**Methods:**

This is a prospective, multicenter, cohort study, which will recruit a total of 4000 participants over 50 years from 12 research centers with different altitudes (50m~3500m). The study will consist of a baseline assessment and a 5-year follow-up. Participants will undergo assessments of demographic information, anthropomorphic measures, self-reported questionnaires, handgrip muscle strength assessment (HGS), short physical performance battery (SPPB), blood sample analysis, and imaging assessments (QCT and/or DXA, US) within a time frame of 3 days after inclusion. A 5-year follow-up will be conducted to evaluate the changes in muscle size, density, and fat infiltration in different muscles; the muscle function impairment; the decrease in BMD; and the osteoporotic fracture incidence. Statistical analyses will be used to compare the research results between different altitudes. Multiple linear, logistic regression and classification tree analyses will be conducted to calculate the effects of various factors (e.g., altitude, age, and physical activity) on the skeletal muscle system in a high-altitude environment. Finally, a provisional cut-off point for the diagnosis of sarcopenia in adults at different altitudes will be calculated.

**Ethics and dissemination:**

The study has been approved by the institutional research ethics committee of each study center (main center number: KHLL2021-KY056). Results will be disseminated through scientific conferences and peer-reviewed publications, as well as meetings with stakeholders.

**Clinical Trial registration number:**

http://www.chictr.org.cn/index.aspx, identifier ChiCTR2100052153.

## Introduction

Osteoporosis has become a public health concern with the rate of aging in the global population increasing (1). Identifying the risk factors for osteoporosis could help prevent the condition’s development. Environmental factors (such as altitude, sunlight, and temperature) have been proposed to influence bone mineral density (2). Basu M et al. found proximal phalanx bone impairment in healthy males who migrated from an altitude of 3542m to an extreme altitude (5400–6700m) in India where they stayed for 4 months (3). A Chinese study reported that people living in Tibet have lower spine bone mass compared with people who live at low altitudes (4). An animal experiment also showed that bone mass was significantly and negatively affected by exposure to a high-altitude environment. With the increase in altitude (1850~5450m), negative changes in the morphometric and geometric properties of the femur were observed (5). The loss of bone mass and/or decrease in bone density is the main manifestation of osteoporosis. As expected, several studies based on large sample sizes have found that highlanders have a higher risk of osteoporosis (6) and are more likely to suffer hip fractures (7–9). The above research results may be related to the mechanism that high altitude-induced hypoxia may stimulate the secretion of many hormones that have affected bone mineral metabolisms (3, 10). For example, activities of bone-specific alkaline phosphatase and 25(OH) vitamin D were both found to decrease significantly in the high-altitude area (3). Notably, the relationship between high altitude and bone status is still insufficient. Existing studies are also limited by their designs for certain people and/or small sample sizes. In particular, some studies only included narrow-altitude ranges (about 100~200 m), which restricts effective comparisons between distinct altitudes. This can sometimes lead to conflicting results (9, 11). A reasonable and wider range of elevation comparison design can contribute to explore the effect of hypoxia on bone and reveal the potential effective threshold. So far, no studies have been conducted in China on the prevalence of osteoporosis in the general population in high-altitude areas. More studies, especially longitudinal cohort studies, are essential to investigate the prevalence of osteoporosis and the potential risk factors for bone mass loss in the plateau area.

Hypoxia causes complex angio-adaptive and endocrine adaptations in skeletal muscle, resulting in the growth, stabilization, or regression of muscle capillaries as well as changes in blood biochemical markers (e.g., significant reductions in plasma leptin and homocysteine, insulin, and C-reactive protein) (12, 13). High-altitude hypoxic environments have been demonstrated to influence a person’s body composition (e.g., reductions in body weight, fat-free mass, fat mass, muscle mass, and/or body water) (14–17). Studies have been conducted on the relationship between altitude and muscle or body function, particularly in sports training. Altitude hypoxia training has become a popular means to increase endurance athletes’ performance for decades (18–22). What’s more, current research indicates that chronic intermittent hypoxic–hyperoxic periods exposure at rest is beneficial for older patients with cardiovascular and metabolic diseases or cognitive impairment to improve physical and cognitive performance and reduce cardiometabolic risk factors (23). Despite much research in this area to date, the results are highly controversial as intraindividual and interindividual variabilities (24, 25). More studies are needed to confirm and extend the evidence.

The loss of muscle mass, strength, and/or physical function is often referred to as sarcopenia, which is closely related to adverse clinical outcomes (15–17). Sarcopenia will have a major impact on the Asian aging population (26). The diagnosis of sarcopenia is also highly variable due to race, measurement methods, and living environments (27, 28). High-altitude hypoxia is considered to be able to facilitate sarcopenia and fat distribution (26, 29, 30). Chinese studies indicated that the incidences of sarcopenia in the high-altitude population (altitude>3500m and altitude at 2260m) were significantly higher than those in the plain population (26, 31). Specific cutoff values established according to altitudes for sarcopenia in the plateau populations seem more reasonable. However, very limited relevant studies are available. The assessment of muscle mass is a crucial element in diagnosing sarcopenia. Bioelectrical impedance analysis (BIA) or dual X-ray absorptiometry (DXA) were the most commonly used methods in the past. Nevertheless, the correlation of muscle mass with muscle strength, and more generically, with muscle function is low, and this discrepancy may be partially related to the presence of fatty infiltration (32, 33). The recent European Working Group on Sarcopenia in Older People recently replaced “low muscle mass” with “low muscle strength” as a primary determinant of sarcopenia (34) implying that muscle mass based on DXA and BIA may not be sufficient in the detection of sarcopenia and that methods with higher sensitivity in sarcopenia screening are warranted. Skeletal muscle area based on segmentation technology and muscle density measured by quantitative computed tomography (QCT) were considered to be more promising in the assessment of sarcopenia (35–37). However, the sarcopenia definition based on CT assessments of muscle size and density is lacking.

The musculoskeletal system operates as a finely coordinated unit, interconnected not only by mechanical aspects but also by humoral factors. Muscle seems to possess the “upper hand” in its relationship with bone (38). Muscle loading induces a range of biomechanical signals necessary for bone growth and remodeling. Also, osteoporosis or fractures will lead to muscle atrophy and muscle mass reduction (38). Indeed, several muscles and bone-derived hormones (e.g., leptin, insulin, GH/IGF-1, myostatin, FGF2, and sexual steroids) are under active investigation to better explain the complex cross-talk and discrete hormonal influences between muscle and bone (38). Therefore, simultaneous assessment of bone and muscle may help gain a more complete picture of disease prevention and treatment in a certain area.

High altitude is generally defined as an altitude higher than 1500m above sea level, which is further classified into three grades: high altitude (1500-3500m); ultra-high altitude (3500-5500m); and very high altitude (>5500 meters) (39). The main environmental stressor associated with high altitude is decreasing atmospheric oxygen pressure. Other environmental stressors include low temperatures, humidity, and increased ultraviolet radiation (40). The impact of altitude on the musculoskeletal system is diverse and contingent upon the altitude in question. Existing studies are limited by their designs for comparison between two altitudes (26, 41). As a result, studies at different altitudes cannot be directly compared. Multi-altitude control studies can comprehensively depict the changes in the musculoskeletal system at different altitudes.

As a province with an altitude fluctuation ranging from less than 100 meters to more than 3,000 meters, Yunnan province has a particular advantage in the study of the effects of altitude on osteoporosis and sarcopenia. This study is a multi-center cohort study in 12 regions where the altitude fluctuations range from 50 to 3500 meters. The primary aims of this study are listed as follows: Firstly, to compare the baseline prevalence of osteoporosis and sarcopenia in the over-50-year-old population at different altitudes and establish a provisional cut-off point based on QCT for the diagnosis of sarcopenia in adults according to altitude. Secondly, the bone and muscle characteristics of people at different altitudes are compared, such as bone density, muscle mass, muscle density, and biological indicators. Thirdly, follow up for 5 years and compare the incidence of adverse events (fall, osteoporosis fracture, death, etc) at different altitudes. The secondary study aims to explore the effect and mechanism of a high-altitude environment on the skeletal muscle system.

## Methods and analysis

This longitudinal cohort study aims to investigate the prevalence of osteoporosis and sarcopenia in Yunnan Province. Multicenter control at different altitudes can give insight into how altitude affects bone and muscle.

### Study design

The sarcopenia and osteoporosis study in Yunnan province (SOY study, Trial registration number: ChiCTR2100052153) is a multicenter, prospective, cohort study. The study protocol consists of three main steps: recruitment, a baseline visit, and five years follow-up visit (**Figure1**).

**Figure 1 f1:**
[figure not shown]
Flow chart of study design and procedures. SPPB, short physical performance battery. The analysis outcomes included: the changes in muscle size, density, and fat infiltration in different muscles, the decrease in BMD, the muscle function impairment, and the osteoporotic fracture incidence during a five-year follow-up period.

### Recruitment strategy

The enrolment of potential subjects is assessed by investigators at each clinical center according to the inclusion and exclusion criteria. Each subject will sign an informed consent form before officially entering the study. The subjects of the SOY study are enrolled in 12 centers at different altitudes (**Figure 2**). The inclusion criteria are that participants should be aged over 50 years old and living at the research site for more than 10 years. Exclusion criteria were as follows: a. Inability to stand or walk independently; b. Deformity of the lumbar spine and hip joint; c. Tumors treated with radiotherapy or chemotherapy; d. Patients with metallic implants *in vivo*; e. Other serious or life-threatening diseases (e.g. severe stroke). Recruitment will start in August 2022 except for the main study center the First People’s Hospital of Yunnan Province in which recruitment started in April 2021. Baseline visits and follow-up details are shown in **Table 1**.

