**Figure 2 f2:**
[figure not shown]
Recruitment centers and specific altitude.

**Table 1 T1:** Items and procedures of the study at baseline and each follow-up.

	Baseline	1 year ± 30 days	2 years ± 30 days	3 years ± 30 days	4 years ± 30 days	5 years ± 30 days
Informed consent	X	–	–	–	–	–
Questionnaire survey	X	X	X	X	X	X
Muscle strength assessment (HGS)	X	X	X	X	X	X
Short physical performance battery (SPPB)	X	X	X	X	X	X
QCT scan	X	X	X	X	X	X
DXA scan	X^*^	X^*^	X^*^	X^*^	–	X^*^
Ultrasonic	X^*^	X^*^	X^*^	X^*^	–	X^*^
Blood collection	X^*^	X^*^	X^*^	X^*^	X^*^	X^*^

X, an item that will be collected.

X^*^, item that will be selectively carried out in viable centers.

-, item that will not be collected.

Ethical approval for the cohort study is obtained from the ethics committee of each study center [Main study center-The First People’s Hospital of Yunnan Province No. KHLL2021-KY056]. The study is conducted by ethical principles according to the Declaration of Helsinki. Radiation safety and protection measures are strictly implemented throughout the study. Informed consent is obtained from each participant at the nearest participating imaging center.

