### The estimation of sample size

The sample size necessary for this study is set at 4000. The overall prevalence of osteoporosis at the femoral neck in adults aged above 50 years was reported to be 16%, or even up to 30% in postmenopausal women (29, 42). The overall prevalence of sarcopenia was reported to range from 5.5% to 25.7% (30). Thus, the number of 4000 is set to get the estimated overall prevalence of osteoporosis to be within 5% of the prevalence in the real world and considering the attrition rate of about 10%. This number is also needed to detect a significant difference (at least 5%) in prevalence proportions between the highest level of altitude and the lowest one. This number is also needed to detect significant results from the prospective cohort (survival analysis) with a two-tailed level of significance of 5% and statistical power of 80% when a risk factor for osteoporotic fracture is assumed to exist in 20% of participants at baseline and to increase a background fracture risk of 6% by 50% during the 5-year follow-up period. The SPSS 26.0 software (IBM, Armonk, NY, United States) will be chosen. The level of significance desired for this study is α=0.05, with a power level of β=0.2.

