### Statistical analysis

Baseline cross-sectional analysis between sarcopenia/osteoporosis and altitude will be conducted, including the prevalence, imaging parameters, SPPB, and blood sample indexes of skeletal muscle. The 5-year follow-up data will focus on comparing the rate of skeletal muscle degradation at different altitudes and the incidence of adverse events such as falls and fractures during the follow-up period. One-way ANOVA will be used to compare the research results between different altitudes. Multiple linear and logistic regression analyses were conducted to calculate the effects of various factors (e.g., altitude, age, and physical activity) on the skeletal muscle system in a high-altitude environment. Cox proportional hazards models were used to calculate the strength of BMD, muscle density, and muscle mass to predict the risk of major osteoporotic fractures. Provisional cutoff points based on QCT were defined for the variables used to screen for sarcopenia or osteoporosis using the 20th percentile of their population distributions.

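### The main centre enrols 16 months before the other eleven, and the one-way ANOVA by altitude cannot separate timing of measurement from altitude for season-sensitive cross-sectional measures

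*Protocol article*

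**What the plan says.** All places are in the protocol article.

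- **Recruitment strategy:** "The subjects of the SOY study are enrolled in 12 centers at different altitudes". On timing: "Recruitment will start in August 2022 except for the main study center", "in which recruitment started in April 2021". No end date, duration or enrolment rate is given for any centre.
- **Table 1:** follow-up visits fall at each anniversary from year 1 to year 5, within 30 days either side. Blood collection is marked as an "item that will be selectively carried out in viable centers".
- **Statistical analysis:** "One-way ANOVA will be used to compare the research results between different altitudes". Multiple linear and logistic regression are also planned, to "calculate the effects of various factors (e.g., altitude, age, and physical activity"; the bracket is a list of examples. Calendar period and month of visit are not named.
- **Introduction:** the second primary aim compares bone, muscle and biological indicators across altitudes. Sunlight and temperature are listed, beside altitude, as possible influences on bone mineral density.

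**The concern.** Altitude is a property of the centre, so anything else that differs systematically by centre, including when people are measured, enters the altitude contrast directly. One centre can enrol for 16 months with no concurrent observation at any other altitude. A one-way ANOVA has a single factor and no place for date or month.

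If a measure varies with season or calendar period, part of the difference between the main centre's altitude and the others could be a timing difference. The exposed comparisons are cross-sectional ones of biological indicators and activity, and the former belong to a primary aim. That 25(OH)D, PTH, turnover markers and IPAQ activity vary with season is an assumption here; the article does not say so.

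**Working it through.** The article states no figure on this point. Its sample size ("The sample size necessary for this study is set at 4000") neither drives the concern nor is changed by it.

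**1. Length of the gap** (start dates from Recruitment strategy). April 2021 to August 2022: (2022 − 2021) × 12 + (8 − 4) = 16 months, for 1 centre of 12. The other 11 share a start month.

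**2. Season, under an assumed cycle.** Assume an effect A·cos(2π(t − 8.5)/12), where t is in months, 1 August is t = 8 and the peak is in mid-August. The mean over an enrolment window from a to b is A × (12/2π) × [sin(2π(b − 8.5)/12) − sin(2π(a − 8.5)/12)] / (b − a), with 12/2π = 1.910.

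- Later centre filling August to October (8 to 11): 1.910 × (0.966 + 0.259)/3 = 0.78, so +0.78A.
- Main centre recruiting evenly April 2021 to July 2022 (4 to 20): 1.910 × (−0.259 + 0.707)/16 = 0.05, so +0.05A.
- Any centre recruiting evenly over 12 months: 0.

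The contrast in the first pattern is 0.78A − 0.05A = 0.73A, or about 0.3 SD if A is assumed to be 0.4 SD. If all centres recruit evenly over 12 months, it is zero.

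**3. How extreme the first pattern is.** On an assumed equal split, 4000/12 ≈ 333 per centre. Filling in three months means 333/3 = 111 a month at each later centre, against 333/16 ≈ 21 a month at the main centre.

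**4. Calendar period, under an assumed shift.** Suppose the main centre's mean differs by d SD through period alone and it supplies a share w of its altitude group. The group mean then moves by w × d.

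- d = 0.05, w = 1/12: 0.004 SD.
- d = 0.20, w = 1/2: 0.10 SD.
- w = 1 (one centre per altitude level): the full d.

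**5. Effect on a linear altitude slope.** Assume 12 equally weighted centres, evenly spaced from 50 to 3500 m. Spacing is 3.45/11 = 0.3136 km, and the sum of squared deviations is 0.3136² × 143 = 14.07 km². A shift d at one centre moves the slope by d × (its deviation)/14.07.

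- Main centre at an extreme: 1.725/14.07 = 0.12d per 1000 m.
- Main centre next to the middle: 0.157/14.07 = 0.01d per 1000 m.

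The main centre's altitude is in Figure 2, which is not shown, so its place in this range is unknown.

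**6. Which outcomes are exposed.**

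- *Cross-sectional values at a visit:* exposed, if the measure varies with season or period.
- *Within-person change:* anniversary visits return each participant to about the same season, so a stable seasonal effect largely cancels.
- *Falls:* the SARC-F item asks about the past year, and follow-up falls accumulate over the whole period. Both cover all seasons.
- *Fracture incidence:* likewise accumulated over the follow-up period.

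**The case against.** The strongest reply is that no imbalance is demonstrated. Eleven centres share a start month, so the documents show no link between period and altitude among them. The main centre may also go on recruiting after August 2022. Season of enrolment depends on a duration that is not given, and the 0.73A contrast needs a pattern found nowhere in the article. The amplitude is assumed too. The regression covariates are only exemplified, and a full list may sit in a document not shown. Blood is drawn only where feasible, so the laboratory measures concern a subset of centres.

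All of this stands, and it rules out several stronger readings that a reader might infer:

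- *That period and season are tied to altitude across the study.* Only one centre is offset, and only for participants enrolled before August 2022.
- *That the anniversary windows carry the error through follow-up.* They largely protect the change outcomes.
- *That falls are affected.* They are counted over whole years.
- *That nothing in the plan adjusts for timing.* This is certain for the ANOVA only.
- *That QCT measures are affected because the main centre was calibrated, or its staff trained, earlier.* The article does not date these steps by centre and reports no drift.

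What the reply does not remove is that one-way ANOVA is the stated method for comparing altitudes. It cannot hold month or date, whatever an unseen document adds to the regressions.

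**Conclusion.** The concern holds in a limited form. For main-centre participants enrolled before August 2022, calendar period coincides with that centre's altitude, and season may differ between centres if they fill at different speeds. The one-way ANOVA cannot separate either from altitude. This matters only for cross-sectional comparisons of measures assumed to vary with season: 25(OH)D, PTH, turnover markers and IPAQ activity.

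The size cannot be computed from the article. The seasonal contrast lies between about zero and 0.73A in the two patterns worked through, and the upper value rests on an extreme enrolment pattern. The period shift depends on an unknown d and on the main centre's share of its altitude group. The direction is also unknown. This is a worthwhile refinement of a stated method, of minor severity; it is not an error in a figure, and no sample size changes.

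**What to change.** - **Main change.** For 25(OH)D, PTH, turnover markers and IPAQ activity, compare altitudes with the multiple regression already planned in place of the one-way ANOVA. Add month of assessment as one sine and one cosine term, taken from the visit dates that the 30-day windows already require.
- **Sensitivity analysis.** Repeat these comparisons without main-centre participants enrolled before August 2022. This addresses calendar period, which month terms do not. State in advance that it may remove much or all of that centre and its altitude: if the main centre stopped recruiting by July 2022, none of its participants remain.
- **Limit to state.** Month terms can separate season from altitude only as far as enrolment months overlap between centres or vary within them. Tabulating enrolment month by centre would show this.

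**Cost.** Two covariates and one extra analysis, with less precision at the main centre's altitude in the latter. No procedure, visit or sample size changes. If enrolment proves even over the year, the adjusted and unadjusted results should agree closely and little is lost.
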